# Comparative evaluation of the efficacy of customized maxillary oral appliance with mandibular advancement appliance as a treatment modality for moderate obstructive sleep apnea patients—protocol for a randomized controlled trial

**DOI:** 10.1186/s13063-022-06070-w

**Published:** 2022-02-16

**Keywords:** Apnea/hypopnea index, Continuous positive airflow, Customized maxillary oral appliance, Mandibular advancement device, Obstructive sleep apnea, Polysomnography

## Abstract

**Background:**

Obstructive sleep apnea (OSA) is due to the obstruction of the upper airway during sleep. This condition is often associated with multiple symptoms and co-morbidities. There are many treatment options mentioned in the literature to manage OSA, among which interventional option of continuous positive airflow (CPAP) and non-interventional option, i.e., mandibular advancement device (MAD), which is an oral appliance (OA), are the most preferred ones. This study aims to evaluate the efficacy of customized maxillary oral appliances with mandibular advancement devices in moderate OSA patients.

**Methods:**

A prospective interventional study with a randomized controlled trial will be carried out involving 40 participants (sample size), with an apnea-hypopnea index (AHI) > 15–30, recorded on polysomnography (PSG). Study participants will be randomly divided into the following treatment groups: control group or group subjected to mandibular advancement device (MAD, *n*=20) and second group subjected to customized maxillary oral appliance (CMOA, *n*=20). Baseline assessment of apnea/hypopnea index (AHI), oxygen saturation in blood, percentage of rapid eye movement, electroencephalogram, electrocardiogram, oro-nasal airflow via a pressure transducer, and Epworth Sleepiness Scale will be done. Then both study group participants will receive their respective appliances. And after one month and three months of delivery of the appliance, all the parameters, i.e., AHI, oxygen saturation in blood, percentage of rapid eye movement, electroencephalogram, electrocardiogram, oro-nasal airflow via a pressure transducer, and Epworth Sleepiness Scale will be re-evaluated and compared with the baseline measurements. Descriptive and analytical statistics will be done. SPSS (Statistical Package for Social Sciences) Version 20.1 will be used as statistical software. The statistical significance between the two groups after one month and three months will be evaluated at *p*< 0.05.

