**Enrolment:**				
Eligibility screen	X			
Informed consent	X			
Screening	X			
Baseline data collection	X			
Randomize subject allocation	X			

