### Allocation concealment mechanism

Upon confirmation of eligibility (patients must meet all inclusion criteria and must not meet exclusion criteria), the clinical site will contact a centralized internet randomization system (https://randomizer.at/). Patients will be randomized using block randomization to one of the two arms, MAD arm or CMOA arm.

Generation of allocation sequence, enrolment of participants, and assignment of participants to interventions will be performed by authors in the Department of Sleep Medicine, DMIMS (DU).

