## Intervention

### Mandibular advancement device (MAD) Fig. 2

MAD will be fabricated for the Control Group. An impression of upper and lower jaws will be made for all the participants of this group and will be poured to form a cast. A protrusion index will be recorded using a George Gauge by protruding the mandible to 50% of the maximum protrusion. (roughly 6 mm). The appliance will have an upper and lower part of the elastomer and will be interconnected with a screw that will be tightened by advancing the mandible by 6 mm from its centric position. Symptoms related to temporo-mandibular disorder (TMD) will be evaluated. All the patients will be advised to wear the appliance daily while sleeping at least for 6 h.

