#### Fabrication

Impressions of the upper and lower arch of the second group to be treated with the CMOA will be recorded. The cast obtained from the impression will be scanned for CAD designing with the help of CAD software. The design will be 3D printed in polymethylmethacrylate (PMMA ) material and will be delivered to the patient. All the patients will be advised to wear the appliance daily while sleeping at least for 6 h.

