### Investigations

#### Polysomnography (PSG)

An overnight PSG will be performed in the Department of sleep medicine before and after one month and three months of intervention by MAD and CMOA. Recording of PSG will be scored as per the guidelines of the American Academy of Sleep Medicine. The event of apnea or hypopnea per hour will be calculated.

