### Outcome measure

#### Primary outcome

The primary outcome will be the change in the score of AHI, SpO2, REM, EEG, ECG, RDI, and ESS from baseline to the end of 1 month of intervention by MAD and CMOA.

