### Safety evaluation

Adverse events (AEs), including AEs related to PMMA allergy, TMJ pain or muscle pain due to an increase in the vertical dimension of occlusion, gag reflex due to extension of appliances in the soft palate, and others will be recorded. For safety assessment, details of all such adverse events will be recorded by a research assistant in the case report form. Any serious adverse events will be reported within 24 h to the Institutional Ethics Committee.

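### Allocation precedes impressions and follow-up is timed from delivery, so a randomised patient who never receives an appliance has no defined outcome assessment

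*Protocol article*

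**What the plan says.** All references are to the protocol article.

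- **Allocation.** Table 1 lists "Randomize subject allocation" in its pre-treatment column. The section on the allocation concealment mechanism sets the trigger: "Upon confirmation of eligibility (patients must meet all inclusion criteria and must not meet exclusion criteria), the clinical site will contact a centralized internet randomization" service.
- **Impressions.** These are described by allocated group. For the control group: "An impression of upper and lower jaws will be made for all the participants of this group". For the other arm, under Fabrication: "Impressions of the upper and lower arch of the second group to be treated with the CMOA will be recorded". The MAD is then made from a cast. The CMOA is scanned, designed by computer, printed and delivered.
- **Visit clock.** The Abstract counts from delivery ("after one month and three months of delivery of the appliance, all the parameters"). The Polysomnography section schedules recordings "before and after one month and three months of intervention by MAD and CMOA". The primary outcome is a change "from baseline to the end of 1 month of intervention by MAD and CMOA".
- **Analysis.** The Statistical analysis section names t-tests or their rank equivalents, and adds inverse probability of censoring weighting for a hypothetical scenario. The data management section handles missing continuous outcomes with a multi-level approach under missing at random, with pattern mixture sensitivity analyses, and requires reasons for withdrawal to be recorded.

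**The concern.** A period of impression-taking and manufacture lies between randomisation and the start of the visit clock. Someone allocated in that period may fail or refuse the impression, leave before the device is ready, or not accept it at fitting. For that person the event that starts the clock never happens, so no follow-up polysomnography falls due and no change from baseline can be formed.

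What is at stake is the comparison of groups as randomised. If patients without a device also have no outcome, each arm is represented by those who could be fitted, and fitting happens after allocation. With 20 patients per arm, a few such losses carry weight. An analysis plan can define a population, but it cannot recover a sleep recording that was never scheduled. The visit anchor and the order of steps therefore have to be settled in the protocol.

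**Working it through.** The article gives no rate of pre-delivery loss and no outcome for patients without a device, so there is no figure to reproduce. The check is of sequence, then of what each stated analysis does with such a patient.

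**Step 1: order of events.** Eligibility confirmed → allocation (Table 1; allocation concealment section) → impressions by group (MAD section; CMOA Fabrication) → manufacture → delivery → assessments at 1 and 3 months (Abstract; Polysomnography; Primary outcome). For a patient who receives a device, delivery and start of intervention can be read as the same date. For one who does not, neither date exists.

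**Step 2: what the stated analyses do with a baseline-only patient.**
- *t-tests or rank tests:* only patients with a follow-up value enter.
- *Multi-level model under missing at random:* the unobserved course is implicitly taken from patients in the same arm who have follow-up. As the visits are timed, those are patients who received the device.
- *Pattern mixture models:* with no visits in the never-delivered pattern, nothing after baseline informs it, so the result rests wholly on the assumption chosen.
- *Inverse probability of censoring weighting:* patients with follow-up are weighted to stand in for those without. This targets the stated hypothetical scenario, not outcomes as randomised.
- *Recording withdrawal reasons:* explains the loss but supplies no outcome.

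**Step 3: can size or direction be calculated?** Let k of the 20 patients in an arm never receive a device. Let F be the mean change in fitted patients and U the mean change in the others.

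- Mean as assigned = (1 − k/20)·F + (k/20)·U
- Mean as fitted = F
- Difference in that arm = (k/20)·(F − U)

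The error in the between-arm contrast is this quantity for CMOA minus the same quantity for MAD. If F − U is assumed to be equal in both arms, call it g. The error is then (k for CMOA − k for MAD)/20 × g:

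| Never delivered, CMOA | Never delivered, MAD | Error in contrast |
|---|---|---|
| 2 | 0 | 2/20 = 10% of g, one way |
| 0 | 2 | 2/20 = 10% of g, the other way |
| 2 | 2 | 0 |
| 4 | 0 | 4/20 = 20% of g, one way |

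The counts are assumptions chosen to show the range. The article gives neither the counts nor g, so no value or sign follows from it.

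**The case against.** The strongest reply is that nothing in the article removes these patients. They keep a baseline record, a missing-data rule exists with sensitivity analyses beyond missing at random, and a condensed article may leave the analysis population to the full protocol or analysis plan. Timing visits from delivery is also sensible in itself, because it gives fitted patients equal exposure to the device. And some patients who could not be fitted are screened out beforehand: the exclusion criteria cover too few teeth for retention, limited protrusion, severe periodontal disease, joint disorders and uncooperative subjects.

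Much of this stands. The silence on an analysis population is not an error here, and the delivery anchor should stay for patients who receive a device. It does not answer the scheduling gap, because the missing-data methods cannot supply an assessment that the timetable never calls for.

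A reader might draw four stronger inferences, which the document does not support:

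- **That unfitted patients are dropped from their arm.** No section says so. The as-fitted comparison is a consequence of the timing and the methods, not a stated rule.
- **That the bias favours CMOA.** The Safety evaluation section does list "gag reflex due to extension of appliances in the soft palate", and only the CMOA is described with such an extension. But it is listed as an adverse event to record, not as a cause of failed delivery, and the extension is 1 mm.
- **That manufacturing times differ by arm.** Two routes are described, but no durations are given.
- **That power is at risk.** The calculated minimum is 16 per group and 20 are enrolled, so up to 20 − 16 = 4 losses per arm fall within the stated allowance.

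**Conclusion.** The point holds as a fault in step order and visit timing. Randomisation comes before the group-specific impressions, follow-up starts at delivery or intervention, and a randomised patient who never receives an appliance therefore has no defined outcome assessment. The stated analyses would then amount in effect to a comparison of fitted patients.

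This rests on two readings: that impressions described by group are taken after allocation, and that no undisclosed rule dates visits for non-recipients. The size is unknown. In each arm it is the never-delivered share times the gap in mean change between fitted and unfitted patients, and the article gives neither. The direction is equally open. This is a worthwhile, low-cost improvement. It does not show that the trial's result would be wrong.

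**What to change.** 1. Take the upper and lower impressions in all consenting, eligible patients before allocation. Both arms need them, so impression failures and refusals would then fall before randomisation.
2. State that a randomised patient whose appliance is not delivered keeps the 1- and 3-month assessments, timed from the scheduled delivery date, and is analysed in the assigned arm. Fix that date by the same rule in both arms. Keep the actual delivery date as the anchor for everyone else.
3. Report by arm the number never delivered and the interval from randomisation to delivery.

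Earlier impressions do not address gagging when the CMOA is fitted; only the retained follow-up in item 2 covers that.

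The cost is one existing step moved, one sentence on visit timing, and a few impressions in patients who are then not randomised. No sample-size figure changes. The Trial status section anticipated the end of recruitment by June 1, 2021, so item 1 may come too late for patients already allocated. Analysis in the assigned arm and item 3 remain possible.

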**Discussion:**

We expect, customized maxillary oral appliance to be more efficient in managing moderate OSA, in comparison with MAD. If the hypothesis of the present study is confirmed, then this customized maxillary appliance will be quoted as a “gold standard” for managing moderate OSA.

**Trial registration:**

CTRI/2020/07/026936 Registered 31 July 2020.

## Background

Obstructive sleep apnea (OSA) is identified by repetitive events of partial or total blockage of the upper airway during sleep resulting in arterial oxygen desaturation and arousals. This syndrome is often associated with many symptoms and co-morbidities, such as excessive daytime sleepiness, cognitive problems, obesity, type 2 diabetes mellitus, hypertension, exacerbation of the chronic obstructive pulmonary disease, apnea, nocturnal awakening, episodes of choking during sleep, and morning headache [1–3]. Severe OSA has been reported as the greatest risk factor for atherosclerosis, acute myocardial infarction, and general mortality [4].

Literature has documented OSA as an independent risk factor for cardiovascular disease, ischemic stroke, and general mortality. Surveys have proven poor quality of life among patients suffering from OSA, and also significantly higher incidences of industrial and road traffic accidents in them [5].

Polysomnography (PSG) is a diagnostic tool used for OSA. It records the apnea/hypopnea index (AHI) to determine the severity of OSA. Depending on AHI, OAS is classified as mild (AHI 5–15), moderate (AHI > 15–30), or severe (AHI > 30) [6]. Treatment options for OSA are behavioral and surgical weight loss therapies, positional therapy, pharmacological therapy, surgical therapies (Pharyngeal and maxillomandibular surgeries), Continuous positive airway pressure (CPAP), and oral appliances (OA) such as mandibular advancement device (MAD) [7–9]. Among these treatment options except for CPAP and OA, results for other non-surgical therapies are highly unsatisfactory [10]. CPAP is considered to be a gold standard treatment option for patients with OSA. At the same time, the use of CPAP is associated with various problems such as muscle sagging, discomfort to pressure sensation and its leakage, skin inflammation, the loud noise of the machine, and many more, making it noncompliant to the users [11].

MAD has become a viable alternative and the most widely accepted treatment of choice by patients suffering from mild to moderate OAS. Several authors in their studies have concluded that MAD has a good contribution in reducing AHI and in raising the quality of life in such patients when compared with CPAP [12, 13]. MAD works on the principle of clasping the mandible in a forward and downward position that helps to reduce AHI by enlarging the upper airway [14].

However many long-term model analysis studies have reported several side effects of MAD, such as tooth pain, temporomandibular joint disorders, xerostomia or excessive salivation, and gum irritation [15–17]. At the same time, some studies have shown that TMD symptoms in patients using occlusal splint last up to 3–4 months. For most patients, the symptoms disappeared after 5 years [18].

Given the high prevalence of OSA among the population and the side effects of existing appliances, new effective treatment options would be welcomed. The present study focuses on a novel OA named customized maxillary oral appliance (CMOA), to provide a new therapeutic option for patients with moderate OSA. This protocol will help to undertake the study to evaluate the efficacy of this CMOA against MAD for managing mild to moderate OSA.

## Methods

### Ethical aspects

The protocol for the present study was submitted to the institutional Ethical committee. After approval, the study was registered for a randomized controlled trial (RCT). The study participants will be informed about the study and the intervention to be carried out. Signed consent in the local language will be obtained from them before the study starts. The data obtained in the course of the trial will be treated under the applicable Data Protection Law.

A team of 4 members of the Institutional ethical committee will be appointed under Data Monitoring Committee (DMC) is to ensure the ethical conduct of the trial and to protect the safety interests of patients during and after the trial.

In situation wherein termination of the trial if required the Institutional Ethics Committee (IEC) and the Competent Regulatory Authorities will be informed.

The data obtained in the course of the trial will be treated under the applicable Data Protection Law (EU General Data Protection Regulation – GDPR - 2016/679), the Federal Data Protection Act (Bundesdatenschutzgesetz, BDSG), the State Data Protection Act of Baden-Württemberg (Landesdatenschutzgesetz, LDSG BW) as well as § 40 (2a) AMG.

During the clinical trial, patients will be identified solely utilizing an individual identification code (Patient ID). Storage of trial findings on a computer will be done by local data protection law and will be handled in the strictest confidence.

### Protocol amendments

If the trial protocol has to be changed substantially after approval, a written amendment will be required that must be signed by the same persons as mentioned in the trial protocol. Any protocol amendment will only be implemented after approval has been granted by the IEC and the competent authorities. Any substantial protocol amendment affecting the benefit-to-risk ratio must be approved by the responsible EC will be notified. Participants will be informed about relevant changes in the trial and will be asked to re-consent in writing.

### Study design (Fig. 1, Table 1)

The present study is a randomized, controlled, parallel, and two-armed (i.e., MAD and CMOA), clinical trial. The duration of the study will be for one year. The patients reporting to the Department of Sleep Medicine, which are diagnosed cases of moderate OSA will be considered as participants for this study.

**Fig. 1 Fig1:**
[figure not shown]
Flowchart of the study

**Table 1 Tab1:** SPIRIT (Standard Protocol Items: Recommendations for Interventional Trials)

Timepoint	Pre-treatment	Treatment	Post-treatment	
			1 month	3 month
**Enrolment:**				
Eligibility screen	X			
Informed consent	X			
Screening	X			
Baseline data collection	X			
Randomize subject allocation	X			
**Interventions:**				
MAD		X		
CMOA		X		
**Assessments:**				
Primary outcome			X	
Secondary outcomes				X

The study involves 40 sample sizes. At 80% power of the study, the minimum sample size calculated for each group is 16. However, 20 samples in each group will be selected to minimize errors and to cover any loss of cases during follow-up.

These 40 participants will be randomized by creating a computer-generated randomization list. Participants will be assigned random numbers based on consecutive enrolment into group 1 or a control group subjected to MAD (*n*=20) and another group, i.e., group 2 subjected to CMOA.

### Inclusion criteria

The patients diagnosed with moderate OSA (apnea/hypopnea > 15–30 events/hour)Patients were non-compliant to CPAP and refused surgical intervention.Age ranging from 30 to 50 yearsBMI (range 17–39 kg/m^2^)

### Exclusion criteria

The patient diagnosed with severe OSAThe patient diagnosed with mild OSAUncooperative SubjectsPatients with severe periodontal diseasesAn edentulous arch, or without a sufficient number of teeth for the adequate retention of the appliance.Patients with temporomandibular joint disordersPatients with pathologic evidence of airway obstruction.Patients with maximal protrusion of less than 6 mm

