### Customized maxillary oral appliance (CMOA)

#### Design (Figs. 3, 4 and 5)

The appliances will have a base plate and an upper plate. The base plate will be adapted to the maxillary hard and soft tissues (teeth and hard palate). This plate will be overextended by 1 mm in the soft palate region to support, lift, and prevent its downfall. The upper plate of the appliance is designed over the base plate, keeping a 2 mm gap between the base plates. This gap will be made hollow. The upper plate will have the occlusal anatomy of the maxillary teeth so that it occludes with the mandibular teeth (in present occlusal relation), but at an increased vertical dimension which will be achieved by hollowing the plate. These hollow maxillary upper plates will have a hole in the anterior region, that is in the central incisor area to promote continuous inflow of the fresh air that will be directed to the posteriors region of the tongue. In addition to this, a bulge will be designed on the palatal surface of the upper plate of the appliance in the posterior region to prevent the backfall of the tongue.

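### The printed exclusion list would admit a patient with known PMMA/acrylic hypersensitivity, although the protocol foresees PMMA allergy as a harm and describes only the CMOA as made of PMMA

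*Protocol article*

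**What the plan says.** The Exclusion criteria section of the protocol article has eight items: severe OSA, mild OSA, lack of cooperation, severe periodontal disease, no teeth or too few to retain an appliance, temporomandibular joint disorders, pathological airway obstruction, and "Patients with maximal protrusion of less than 6 mm". Neither this list nor the inclusion list mentions material allergy or gagging.

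Allocation concealment mechanism makes these lists the condition for randomisation: "patients must meet all inclusion criteria and must not meet exclusion criteria". Block randomisation to either arm follows.

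On the CMOA, the Fabrication section says "The design will be 3D printed in polymethylmethacrylate (PMMA ) material and will be delivered to the patient", and the Design section says "This plate will be overextended by 1 mm in the soft palate region to support, lift, and prevent its downfall". On the MAD, the Intervention section says "The appliance will have an upper and lower part of the elastomer".

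Safety evaluation lists the harms to be recorded. They include "Adverse events (AEs), including AEs related to PMMA allergy" and "gag reflex due to extension of appliances in the soft palate".

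**The concern.** A hypersensitivity already in a patient's history can be known before allocation, and the protocol treats PMMA allergy as a foreseeable harm. Under the printed criteria such a patient can still be randomised to a PMMA appliance meant for nightly wear of at least 6 hours. The first stake is avoidable exposure.

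The second is comparative. A patient whose jaw cannot protrude far enough for the MAD is removed before randomisation and never enters the comparison. A patient who cannot wear PMMA would come to light only after randomisation, in the one arm described as using it. That patient would then be untreated, withdrawn or lost for a reason tied to the allocated device.

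**Working it through.** No formula applies to the main point, and the plan gives no figure to reproduce. The check is a reading of the sections against each other.

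1. **Is the hazard foreseen?** Yes. Safety evaluation names PMMA allergy and gagging from extension onto the soft palate.

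2. **Which arm does it belong to?** Safety evaluation does not name an arm. PMMA is stated only for the CMOA (Fabrication), and so is the 1 mm overextension in the soft palate region (Design). The MAD is described as elastomer. The article does not say outright that the MAD contains no PMMA; it simply names none. On the text, both hazards attach to the CMOA.

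3. **Do the entry criteria use this knowledge?** Of the eight exclusions, one is specific to the MAD (protrusion under 6 mm; the MAD advances the mandible by 6 mm). Three bear on both appliances: temporomandibular joint disorders, too few teeth for retention, and severe periodontal disease. The other four concern OSA severity (two items), cooperation, and airway pathology. None covers material allergy. The cooperation item describes behaviour and cannot fairly be read as an allergy screen.

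4. **Is there another barrier before allocation?** None is described. Table 1 lists an eligibility screen and a screening step without stating their content.

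5. **What is the chance of receiving the PMMA device?** With 20 of 40 places in the CMOA arm, 20/40 = 1/2.

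6. **How much room is there for loss?** The Study design section gives a minimum of 16 per group and plans 20, so the allowance is 20 − 16 = 4 per arm, or 4/20 = 20%. One such loss in the CMOA arm uses 1/4 of it. That arm falls below 16 only if more than 4 patients are lost for all reasons together. With no prevalence for PMMA hypersensitivity or severe gagging in the article, the expected number of such losses cannot be derived.

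**The case against.** The strongest reply is that this is an omission, not an error. Recording an anticipated adverse event does not contradict leaving it out of the exclusions, and a journal article may condense a fuller protocol that has a hypersensitivity criterion. It is true that the sections do not strictly contradict each other, and that a fuller protocol could hold such a criterion. But both eligibility lists are printed as lists and are applied as the condition for randomisation, and nothing in the article points to further criteria. The gap therefore stands on the text shown.

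A reader might also infer more than the document supports, in four ways.

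- **That gagging should be screened in the same way as allergy.** The article describes gagging as an effect of the appliance, not as a pre-existing trait. It may be part of how tolerable the CMOA really is, and excluding such patients would favour those who can tolerate the experimental device. Gagging at the impression is no basis for the claim either: impressions are described by allocated group, so after assignment, and the MAD also needs an upper impression.
- **That the list protects the MAD arm only.** The asymmetry is partial. Three exclusions bear on both arms, and Safety evaluation itself links joint or muscle pain to increased vertical dimension, which is a CMOA feature.
- **That the comparison will be biased.** The article does not say that patients who react to or gag on the device go unassessed. For missing data it plans a multi-level approach assuming missing at random, with pattern mixture models as sensitivity analyses (Data management/handling with missing data). It also plans inverse probability of censoring weighting (Statistical analysis). These may reduce the effect of device-related loss, but they do not prevent the exposure.
- **That a particular share of the CMOA arm is affected.** The article supports no such figure.

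**Conclusion.** The point holds for known PMMA/acrylic hypersensitivity. The article foresees the harm and ties the material to one arm, yet it prints an entry list that does not remove a patient already known to be at risk. Whether a known severe gag reflex should be treated likewise is a judgement for the investigators, not a defect that the text establishes.

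The size is unquantified. The number affected is unknown, and differential loss is possible but not demonstrated. The case for changing the list is that an avoidable exposure can be prevented at little cost; it does not depend on any prevalence. It rests on two assumptions: that the printed lists are the complete entry criteria, and that the MAD contains no PMMA, as its description suggests.

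**What to change.** Reconcile Exclusion criteria with Design, Fabrication and Safety evaluation:

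- Screen for known PMMA/acrylic hypersensitivity from history, before randomisation, and apply the result equally to both arms so that the groups remain comparable.
- Have the investigators decide, and state, whether a known severe gag reflex belongs in the list too. If so, it should be taken from history only, with no screening impression or palatal test, since either would be a new procedure.
- Keep both items as adverse-event prompts for new cases.
- Report allergy- and gag-related withdrawals by arm, including for participants already enrolled.

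The cost is a short eligibility amendment, with the ethics approval that the Protocol amendments section requires, and one history question, or two if gagging is added. There may be a few more screen failures and a slightly narrower population, which should be stated with the results. The sample size of 20 per arm need not change.

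Timing limits the benefit. The Trial status section reports 20 of 40 participants included by 2 November 2020 and expects recruitment to end by 1 June 2021. An amendment protects only later entrants; for the rest, the reporting by arm is what remains useful.
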